# A multicenter, randomized, double-blind, placebo-controlled trial evaluating the efficacy and safety of Taoren Honghua Jian granule in patients with stable coronary artery disease

**DOI:** 10.1097/MD.0000000000017753

**Published:** 2019-11-01

**Keywords:** randomized controlled trial, stable coronary artery disease, Taoren Honghua Jian granule, traditional Chinese medicine

## Abstract

Supplemental Digital Content is available in the text

## Introduction

1

Coronary artery disease (CAD) is a slowly progressive disease and the most common reason of death globally, responsible for 17.9 million deaths in 2016, representing 31% of all global death causes.^[1]^ It has been certified that inflammation plays an important role in the whole progression of CAD.^[2]^ Beneficial lifestyle and guideline-recommended treating strategies are suggested for all stable CAD (SCAD) patients to reduce morbidity and mortality.^[3]^ However, the existing medical methods could not solve this disease perfectly, even the benefit from initial percutaneous transluminal coronary intervention remains undefined.^[4]^ Thus, the therapeutic choice should be more careful and optimal.

In recent years, the herbal medicine as an alternative method has been demonstrated to treat SCAD and prevent relapse effectively, even in inflammation control.^[5–8]^ According to the theory of traditional Chinese medicine (TCM), pathogen of SCAD can be considered as stagnant Qi and blood. To deal with SCAD and the inflammation, Taoren Honghua Jian granule (THJG) was ascertained by numbers of TCM physicians in China, using *Prunus persica* and *Flos carthami* as the principal element, and *Rhizoma corydalis*, *R chuanxiong*, *Radix paeoniae rubra*, *R salviae miltiorrhizae*, *R angelicae sinensis*, *R rehmanniae*, *Pericarpium citri reticulatae viride*, *R cyperi*, and *Olibanum* as adjuvant components (details in Table 1). THJG has significant influence on inhibition of platelet and improvement of hemorheology in SD mice without triggering any side effect,^[9]^ suggesting the therapeutic potential of THJG against human SCAD. Although, this efficacy should be confirmed with more examines.

**Table 1 T1:**
[figure not shown]
Components of THJG.

We will conduct a well-designed randomized, double-blind, placebo-controlled trial to assess the usefulness and safety of THJG on SCAD. The outcomes of this clinical research could substantiate the value of THJG to improve symptoms and inflammation of SCAD patients. To ensure the quality during the whole trial, we will use THJG, raw extraction of THJG decoction, to substitute medicinal broth. This protocol was finished in September 1, 2019 (Version 1.0).

## Methods/design

2

### Study design

2.1

This is a multicenter, randomized, double-blinded, placebo-controlled clinical trial with 2 parallel arms. The purpose of this research is to estimate the effectiveness and safety of THJG combined in administrate SCAD symptoms and inflammation. Altogether, we will recruit 80 patients with SCAD from 3 hospitals in China: LongHua Hospital affiliated to Shanghai University of Traditional Chinese Medicine, Shanghai Seventh People's Hospital, Gongli Hospital of Shanghai Pudong New Area, Shanggang Community Health Service Center of Shanghai Pudong New Area. Eighty participants will be randomized into THJG group or placebo group according to patients’ included sequence number equally. Patients in THJG group will take THJG (18.3 g, twice a day, orally) for continuous 4 weeks, while patients in placebo group will take THJG placebo (18.3 g, twice a day, orally) for the same duration. The Standard Protocol Items: Recommendation for Interventional Trials SPIRIT 2013 Checklist (Supplementary Material file 1).

### Ethical issues

2.2

The trial will be planned in compliance with the Declaration of Helsinki and Ethical Guidelines for Clinical Research, and the trial protocol has been permitted by the Research Ethical Committee of LongHua Hospital affiliated to Shanghai University of Traditional Chinese Medicine (approval number: 2019LCSY008), Gongli Hospital of Shanghai Pudong New Area (approval number: 2019-023), Shanggang Community Health Service Center of Shanghai Pudong New Area (approval number: 20190610). Additionally, the protocol has been registered on Chinese Clinical Trial Registry (ChiCTR1900021772). The personal information about the potential and enrolled participants will be collected to be used only in this trial, and we will not share or maintain the personal information when unnecessary.

### Study participants

2.3

Participants will be recruited from 3 hospitals (LongHua Hospital affiliated to Shanghai University of Traditional Chinese Medicine, Gongli Hospital of Shanghai Pudong New Area, Shanggang Community Health Service Center of Shanghai Pudong New Area). Recruitment posters and social application advertisements will be proclaimed. The objective, approaches, and potential side-effects and advantages of this research will be explicated utterly to the participants before participants signing informed consent. The planned enrollment period is 15 months.

## Criteria

3

### Main inclusion criteria

3.1

1.Meet the diagnostic criteria for SCAD.^[10]^2.Up to the standard type of TCM type: stagnant Qi and blood.3.Patients aged 18 to 70 years.4.Patients who volunteer to participate in this trial and sign the informed consent.

### Main exclusion criteria

3.2

1.Acute myocardial infarction and other heart disease, such as severe cardiac neurosis, diabetic cardiomyopathy, immune cardiomyopathy, etc.2.With severe chronic or uncontrolled diseases may lose the participant.3.Allergic constitution or allergic to THJG or has serious adverse reactions.4.With opioid analgesic, sedative hypnotic drug, and alcohol abuse history.5.Serious liver or kidney function damage.6.Pregnancy, or have no plans of pregnancy, or feeding women.

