### Quality control

5.6

Longhua Hospital affiliated with Shanghai University of Traditional Chinese Medicine (http://www.longhua.net/ywsy/gzlc/287.jhtml) is responsible for quality controlling and training for all investigators.

At the beginning of this trial, physicians, nurses, and laboratory personnel from 3 research centers will receive systematic training together to completely apprehend the procedure of the whole study. As the trial starts, a trained investigator will be sent to each center every week to check the following:

(1)Number of recruited participants in each center.(2)Included SCAD patients meet the inclusion criteria and do not meet the exclusion criteria.(3)All the participants have signed the informed consent and follow the study process.(4)Clinicians have written the CRFs in time.

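### Exclusion criterion 6 contradicts itself: its middle limb excludes people who are not planning a pregnancy and leaves a woman who is planning one eligible

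*Protocol article*

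**What the plan says.** Section 3.2 (Main exclusion criteria) of the protocol article gives, as its sixth and last item, "Pregnancy, or have no plans of pregnancy, or feeding women". The three conditions are joined by 'or', so meeting any one of them excludes a candidate.

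Section 3.1 (Main inclusion criteria) sets the age range as "Patients aged 18 to 70 years". It places no condition on sex, childbearing potential or contraception, so women who could conceive are within the target population.

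Section 5.6 (Quality control) sends a trained investigator to each center every week. One of the four things to be verified is that "Included SCAD patients meet the inclusion criteria and do not meet the exclusion criteria".

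**The concern.** The first and third limbs have an obvious common purpose: to keep a fetus or an infant from exposure to the study product. The middle limb cannot share that purpose as worded. It excludes on the ground that no pregnancy is intended, and it is silent about someone who does intend one.

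Two things are at stake. The first is safety. A woman who may conceive during the four weeks of dosing is not caught by the criterion that seems meant to deal with pregnancy. This applies in both arms, because section 4.1 describes the placebo as made partly (10%) from the active granule. The second is auditability. Eligibility has to be judged the same way by every center and by the person who checks it. A line that works only if its reader mentally corrects it can be corrected differently in different places.

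**Working it through.** No arithmetic applies. The article states no figure on this point, and the criterion feeds into no calculation. The check is a literal reading of the criterion, followed by a search of the article for anything that would override it.

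**Step 1. Status of each type of candidate under criterion 6 as printed**

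| Candidate | Limb met | Status |
|---|---|---|
| Pregnant | first | excluded |
| Breast-feeding | third | excluded |
| Neither, and not planning a pregnancy | second | excluded |
| Neither, and planning a pregnancy | none | not excluded |

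The last two rows are the problem. They run against the first two: the candidate with the lower chance of pregnancy on study is turned away and the one with the higher chance is let in.

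**Step 2. How far the middle limb reaches.** It has no grammatical subject of its own; the word for women is attached only to the breast-feeding limb. Taken strictly, it would also cover postmenopausal women and men, and so would exclude most of the intended population. That result is absurd, which is evidence that the wording is a slip and not a chosen rule.

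**Step 3. Search for a correction.** The inclusion criteria in section 3.1 contain no rule on sex or contraception. The other five exclusion items do not touch pregnancy. No other section of the article mentions plans to conceive, contraception or childbearing potential. Nothing shown overrides or clarifies the line.

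**Step 4. Is the line operative?** Yes. Section 5.6 makes conformity with the exclusion criteria an item of the weekly check at each center. The line is therefore part of a standard against which enrolled patients are verified, not background text.

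**Step 5. What might have been meant.** At least two origins are plausible: a stray negative in front of the word for plans, or a lost reference to contraception. These give different rules, and the article does not decide between them.

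**Step 6. Effect on the statistics.** The sample size calculation in section 5.7 uses a standard deviation of 7.7, a difference of 4, a 5% two-sided level and 90% power. None of these depends on criterion 6.

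**The case against.** The strongest case on the other side is that nobody would apply the line literally. It stands between two limbs whose purpose is plain, so a clinician would see at once that something is wrong. The article has other language slips, such as an evident misprint in the sign item of the syndrome score in section 5.1.1. Three ethics approvals are listed in section 2.2. The list is headed as the main criteria only, and the protocol that sites work from is not shown, so it may carry the right wording. A weekly eligibility check might also bring the error to light early.

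Much of this stands, and it limits the consequences that can be claimed. A reader might infer that nearly all women would fail screening and the sample would be almost entirely male, or that nearly every woman enrolled would be recorded as an eligibility violation. The documents support neither inference. Both need literal enforcement of an evident slip, and both leave out the most likely course, in which sites apply the meaning they take to be intended and record no deviation. An almost all-male sample also depends on reading the limb as confined to women, which the grammar does not say. Any percentage put on the loss would need a share of women among eligible patients, and the article gives none.

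A reader might also infer that the criterion leaves pregnancy unprotected altogether. It does not: pregnant and breast-feeding women remain excluded, and the gap concerns only women who are neither but plan to conceive.

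The objection does not remove the error itself. Further criteria in a fuller document could add exclusions, but they would not undo one that is already printed. That a careful reader can guess at the intent does not settle which of two different rules was intended.

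**Conclusion.** The point holds as an error of wording in an operative eligibility criterion: the middle limb of criterion 6 contradicts the other two, and following it as printed gives the wrong result for both groups that it sorts. It rests on the printed text alone and needs no numerical assumption.

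Its size cannot be quantified. The effect on recruitment depends on the sex and age mix of candidates and on how sites read the line, and the article reports neither. Sample size, alpha, power, endpoint definitions and the planned analysis are untouched. The reason to correct it is that it bears on who may enter the trial and on whether eligibility can be verified uniformly across centers.

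Two limits apply. A drafting or translation slip is the probable cause, but this is a judgment; the article does not say so. Whether the wording held at the sites has the same fault is unknown.

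**What to change.** The sponsor should:

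- reconcile the middle limb with the other two limbs and with the criterion that the ethics committees approved, and correct the printed text accordingly. The replacement rule, including any time window, should come from the approved criterion and not be guessed from this sentence;
- confirm that all centers, and the investigator who makes the weekly check, hold the same wording;
- re-check the eligibility of any women already screened, whether enrolled or turned away.

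The third step is needed because the correction can no longer be assumed to come before enrolment: sections 5.4 and 6.1 plan recruitment from October 2019, and the article is dated 1 November 2019.

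The cost is a one-line correction, a notification to the ethics committees listed in section 2.2, a circular to the sites and a short review of screening records. No recalculation of the sample size and no change to the analysis is required.

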## Interventions

4

### TCM intervention

4.1

In THJG group, patients will be instructed to dissolve THJG (18.3 g) in 200 mL hot water and take the solution orally twice a day for 4 weeks, while patients in the placebo group will take THJG placebo in the same way.

The THJG will be manufactured, packaged, and labeled by PuraPharm Corporation in Nanning (website: https://www.purapharm.com/zh-hans/). THJG is made from the following ingredients: *Semen persicae* (Taoren, 10 g), *F carthami* (Honghua 10 g), *R corydalis* (Yanhusuo, 10 g), *R chuanxiong* (Chuanxiong, 10 g), *R paeoniae rubra* (Chishao, 10 g), *R salviae miltiorrhizae* (Danshen, 15 g), *R angelicae sinensis* (Danggui, 12 g), *R rehmanniae* (Shengdi, 10 g), *P citri reticulatae viride* (Qingpi, 10 g), *R cyperi* (Xiangfu, 10 g), and *Olibanum* (Ruxiang, 3 g).

*Processing:* Extraction: all the herbs mentioned earlier are put into a water-filled container. After a 30-minute immersion, the mixture is boiled at 100°C for 1 hour. Filter out herbal sediments, and gather herbal filtrate; Concentration: concentrate the herbal filtrate; Granule: mix the concentration with dextrin. The mixture is spray dried to generate dry mash. Then mix the dry mash with magnesium stearate into powders, shattered and screened with a mesh size of 80. Finally, the THJGs are packed in individual bags (18.3 g per bag).

For the control group, THJG placebo contains 90% bitterant, edible lactose, starch, and pigment (such as lemon yellow, caramel pigment, and sunset yellow), are also made from 10% THJG to achieve the similar color, smell, taste, and texture as THJG.

At baseline (Visit 1), patients begin to receive THJG or THJG placebo and laboratory tests. At weeks 2 and 4, patients will visit again (Visits 2 and 3) and perform laboratory tests. Medicine intervention will be finished at week 4. Then at week 8, the follow-up visit (Visit 4) will be taken through a phone call. Every patient should visit and do laboratory tests within 3 days after the original time point.

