#### Integral TCM syndrome score (from baseline to week 4)

5.1.1

Integral TCM syndrome score is a widely used system to evaluate the efficacy of Chinese herb treating SCAD patients, which are stagnant Qi and blood type in China.^[11]^ This assessment form is constitutive of 2 parts: symptom part and sign part. In detail, there are total 8 appraisable items, angina, chest distress, palpitation, vexation, insomnia, lassitude, dizziness, and color of lips and snails, respectively. Each item consists of 4 levels and regarding scores. Wholly, the minimum score is 0 and the maximum score is 33. The higher scores of participants mean a severer condition. The scores and details of TCM syndrome are given in Tables 2 and 3.

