#### Integral TCM syndrome score (from baseline to weeks 2 and 8)

5.2.1

Integral TCM syndrome score from baseline to weeks 2 and 8 will be calculated as one of the secondary outcomes.

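### The week-8 TCM syndrome score includes an inspected sign, but Visit 4 is a phone call, so the week-8 total is not comparable with baseline

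*Protocol article*

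**What the plan says.** All references are to the protocol article.

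- **Visit mode (section 4.1, TCM intervention).** Patients attend in the treatment period: "At weeks 2 and 4, patients will visit again (Visits 2 and 3) and perform laboratory tests". Treatment ends at week 4. For the off-treatment follow-up the text is different: "Then at week 8, the follow-up visit (Visit 4) will be taken through a phone call".
- **Content of the score (section 5.1.1).** "This assessment form is constitutive of 2 parts: symptom part and sign part". The eight items are "angina, chest distress, palpitation, vexation, insomnia, lassitude, dizziness, and color of lips and snails, respectively"; the last word of the eighth item is evidently a misprint for nails. The range is given as "Wholly, the minimum score is 0 and the maximum score is 33".
- **Use at week 8 (section 5.2.1).** "Integral TCM syndrome score from baseline to weeks 2 and 8 will be calculated as one of the secondary outcomes".
- **Recording (section 5.5).** Week 8 is listed among the time points for disease evaluation.
- **Missing values (section 5.8).** Last observation carried forward applies, without saying whether to items or to totals.

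**The concern.** Seven of the eight items are complaints that a patient can describe over the phone. The eighth is the only listed item that someone has to look at. The stated outcome needs all eight items at week 8; the stated visit mode supplies seven. This is a conflict between two things the article does say, rather than a detail left out.

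Week 8 is the only assessment after treatment stops, so it is the trial's only evidence on whether a symptom effect lasts. With no rule for the sign item, sites may handle it differently. One of the available rules, carry-forward, would place an end-of-treatment value into the off-treatment time point.

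**Working it through.** The plan gives no figure for this point, so there is nothing to reproduce. The check sets the sections side by side and then follows each way of handling the item.

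**1. What can be measured at each time point**

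| Time point | Mode (4.1) | Seven complaints | Lip and nail colour |
|---|---|---|---|
| Baseline, weeks 2 and 4 | Attended | Yes | Inspected |
| Week 8 | Phone | Yes | Not inspected |

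No section shown provides for a video call, an attended Visit 4, a self-rating rule for the sign, or a symptom-only score at week 8.

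**2. Weight of the sign item**

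The item tables (Tables 2 and 3) are not shown. Eight items at 0-3 would total 8 × 3 = 24, not the stated 33, so an equal 0-3 weighting is ruled out. Assume that each item has a maximum of 3 or 6, and let k items have maximum 6:

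6k + 3(8 − k) = 33, so 24 + 3k = 33, so k = 3.

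Three items would run to 6 and five to 3. The sign is then worth either

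- 3 points: 3/33 = 9%, leaving 30 points from the complaints; or
- 6 points: 6/33 = 18%, leaving 27 points.

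**3. Effect of each way of handling it**

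Write T for the sum of the seven complaints and S for the sign, with subscripts for the week. The intended change is (T8 + S8) − (T0 + S0).

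- *Sign scored 0.* The recorded change is T8 − (T0 + S0), which differs from the intended change by −S8. Every patient whose sign would still have been present at week 8 shows too large an improvement, by at most 3 or 6 points under the assumption above. Between arms, S0 is balanced in expectation by randomisation, so the contrast reduces to the seven-item contrast. It loses whatever the sign would have contributed.
- *Sign self-reported.* The week-8 value comes from a different rater and method than the baseline value. The size of the resulting error cannot be derived from the document.
- *Sign carried forward as an item.* The week-8 total becomes T8 + S4, an error of S4 − S8. Seven items are fresh; one is an end-of-treatment value.
- *Whole total carried forward.* The week-8 value becomes T4 + S4, so the week-8 change equals the week-4 change, which is the primary outcome. This happens for all 80 patients only if one missing item voids the total and the rule acts on totals.

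**The case against.** The strongest reply is that the article is condensed. The item definitions and the assessment schedule (Table 4) are not shown, and the way one item is collected remotely is an operational matter that the full protocol or case report form may settle. A patient or relative could describe lip colour, or a video call could show it. This limits how far the point can be pressed. It does not remove it: section 4.1 is explicit about the phone call, and a described colour is not the measurement taken at baseline.

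A reader might also infer stronger things that the document does not support:

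- *That no week-8 score can be obtained.* Seven of the eight items can be asked by phone; what is lost is a full total comparable with baseline.
- *That up to 3 spurious points stand against the planned 4-point effect.* The 4 points in section 5.7 are a between-group difference. Scoring the sign 0 shifts change within patients in both arms; it does not add a 3-point bias to the contrast. The 3 points are also only one of two values under the weighting assumption.
- *That all 80 week-8 values would be copies of week 4.* Section 5.8 does not say that carry-forward acts on totals.
- *That the primary result is in doubt.* It is measured at week 4, at an attended visit.

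Finally, the seven-item sub-score is not the full instrument described in section 5.1.1, and an attended or video Visit 4 would keep the 0-33 range. That is a fair alternative, but it changes the stated visit mode and adds burden, whereas the sub-score needs no additional data.

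**Conclusion.** The conflict is real but confined to one item of one secondary outcome at one time point. As written, the week-8 integral score cannot be measured as it is at baseline and weeks 2 and 4, because one of its eight items needs inspection and the visit is by phone. Every patient's week-8 total is affected to some degree. The sign's share is 3 or 6 of 33 points if item maxima are 3 or 6; the true weight is not shown. The direction and size of the error depend on a handling rule that the document does not give. The week-2 score and the primary week-4 analysis stand. The correction should be made before data are analysed, because week 8 is the only off-treatment evidence on this score.

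The conclusion rests on reading the misprinted word as nails, though lip colour alone is enough, and on Table 4 not contradicting the text of section 4.1.

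**What to change.** In section 5.2.1:

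1. Define the week-8 outcome as change from baseline in the seven-item symptom sub-score, computed on the same seven items at baseline.
2. State that the sign item is neither collected nor carried forward at Visit 4.
3. Keep the full eight-item score at weeks 2 and 4, and also report the seven-item sub-score at week 4, so that weeks 4 and 8 can be compared on one scale.

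The cost is a few sentences. All the items needed are already collected, and no visit or patient burden is added. The small downside is that the week-8 score runs over a shorter range than the full instrument (0-30 or 0-27 under the weighting assumption).
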